**Methods:**

A cluster randomized trial will randomly assign 16 clinic regions to either receive PNE training or continue with usual care. Patients with chronic neck or back pain will be enrolled to provide outcome data. Measures will be collected at baseline, 2 weeks, and 12 weeks. The primary outcome will be the Patient-Reported Outcomes Measurement Information System (PROMIS) Physical Function computer-adapted test (PF-CAT). Pre-specified statistical analyses will compare outcomes between clinic regions assigned to PNE treatment or usual care while using random effects to account for region-level clustering.

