## Methods

### Design and setting

This is a two-arm, single-blind, cluster randomized control trial to take place in 16 clinic regions within a large private rehabilitation practice in Atlanta, Georgia and Birmingham, Alabama. Clinic regions are the unit of randomization. We will randomly assign clinic regions to either receive PNE training for physical therapists employed in clinics within the region or usual care (UC) - with no additional training for physical therapists working in the region clinics. The clinic region was chosen over a single clinic for the randomization unit to reduce the potential contamination that may occur when physical therapists work in more than one clinic within a region. Randomization of clinic regions will be stratified by clinic region size and a measure of the region’s clinical outcome for LBP. Clinic region size was based on the average number of new evaluations per week during the period February 2016 – February 2017 over the participating clinics within the designated clinic region. The region’s clinical outcome for LBP is based on the average rank of the region’s clinics among other clinics in the company based on the Oswestry Disability Index [33], a common outcome tool used for LBP. The participating clinics from which the patients will be enrolled have provided permission to carry out this study.

Physical therapists working in clinics in participating regions will receive either PNE training or no additional training based on the random assignment of their clinic region. Outcomes will be assessed on consenting patients with chronic neck or LBP treated within these clinics. We will recruit patients meeting our eligibility criteria who are scheduled for physical therapy evaluation at a clinic within a participating region. Because the intervention is given to physical therapists, potentially eligible patients are asked to consent to provide outcome measures for the study, consistent with a cluster-randomized design. Physical therapists will provide informed consent to participate in the project and participate in training procedures. Other than the training to provide PNE (or not), there will be no attempts to direct physical therapist treatment or duration of care in any way as a result of participation in this study.

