### Statistical methods

Pre-treatment baseline patient and clinic characteristics will be compared between randomized groups to assess chance imbalances. If differences are found, these variables may be included as covariates in sensitivity analyses. In accordance with the intentionto-treat principle, all patients will be analyzed in the group to which their physical therapist was randomized regardless of compliance or fidelity. A “per-protocol” secondary analysis will be considered if fidelity to providing PNE is a concern.

For the primary outcome (PF-CAT), we will apply a linear mixed model to compare the primary PROMIS PF-CAT score at 12 months between the randomized groups while including the baseline PROMIS PF-CAT as a fixed effect covariate, with nested random effects for provider and clinic region to account for clustering by provider and the clinic regions. If substantial imbalances are detected in patient factors at baseline, these factors will be added as additional covariates in sensitivity analyses.

Statistical significance will be evaluating using a 2-sided α = 0.05 for both primary and secondary outcomes without adjustment for multiple comparisons. Intent-to-treat principles will be used for the analysis with all participants analyzed based on the treatment group of the clinic in which they received care - regardless of the therapist’s compliance with providing the PNE intervention. Sensitivity analyses based on fidelity in providing PNE or based on spinal region (neck or low back) may be considered. In addition, we will explore between-group differences from baseline to 2 weeks to examine immediate effects of treatment by a physical therapist trained to provide PNE.

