### Sample size and power calculations

We determined our sample size in order to detect a clinically relevant important effect on the PROMIS PF-CAT after 12 weeks with 80% power while accounting for clustering due to clinic regions. The literature on minimum clinically important differences for PROMIS scores is limited for spinal pain patient populations. In one study of 170 patients with LBP receiving spinal injections, Schalet [46] reported a difference in the mean T-score change of 4.5 vs. 1.7 on the PROMIS PF-CAT for patients reporting they were “better” vs. “worse” with a pooled change score SD of 6.4 (standardized effect size d = 0.43) [46]. Due to the lack of published data on meaningful effect sizes. we examined data from our own healthcare system and found a difference in T-scores for PROMIS PF-CAT of 4.2 vs. 0.72 for patients who reported improved vs. stable back pain based on concurrent Oswestry scores with a pooled SD = 6.9 (standardized effect size d = 0.50). Based on these studies, we will power this study to detect an effect size of d = 0.40. Based on reviews of past cluster randomized trials conducted in primary care settings, we assume an intra-cluster correlation of 0.025 [47, 48] to account for clustering of our primary outcome between the 16 clinic regions. We also assume that the primary outcome will be ascertained in 90% of enrolled patients. Under these assumptions, our cluster randomized design with 316 enrolled patients will provide approximately 80% power with 2-sided α = 0.05 to detect a mean difference in the PROMIS PF-CAT between clinic regions assigned to the PNE and usual care interventions. This calculation does not account for the savings in power that will result from adjusting for the baseline level of the outcome, and is therefore likely to be slightly conservative.

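### The two factors used to stratify the randomisation of regions are absent from the stated primary model; if they are prognostic, the reported standard error is too large and some power is lost

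*Protocol article*

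**What the plan says.** The Design and setting section of the protocol article states: "Randomization of clinic regions will be stratified by clinic region size and a measure of the region’s clinical outcome for LBP". Size is the average weekly number of new evaluations over a one-year period. The outcome measure is the average rank of the region's clinics within the company on the Oswestry Disability Index. The number of levels and the cut-points are not given.

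The Statistical methods section describes the primary analysis as a linear mixed model comparing the randomised groups, "including the baseline PROMIS PF-CAT as a fixed effect covariate, with nested random effects for provider and clinic region". No stratification factor is named there or in any other analysis.

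Further covariates can enter by two routes, both conditional on observed baseline differences and both outside the primary analysis. For patient and clinic characteristics, "these variables may be included as covariates in sensitivity analyses". For patient factors, "these factors will be added as additional covariates in sensitivity analyses".

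**The concern.** Stratifying makes the arms similar on the two factors, so any between-region variance that the factors explain largely drops out of the arm contrast. A model without them does not know this: it leaves that variance in the region-level error and reports a standard error larger than the true one. With 16 regions, between-region variance is an important part of the uncertainty, and the design aims for only "approximately 80% power with 2-sided α = 0.05", so there is little slack.

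The sensitivity-analysis routes do not repair this. Stratification makes imbalance on these two factors unlikely, so the trigger would seldom pick them, and the primary result would be unchanged if it did.

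The outcome rank has a plausible link to the endpoint. In the Sample size and power calculations section, the authors use concurrent Oswestry scores to separate improved from stable patients and find PF-CAT differences of 4.2 against 0.72. That makes a prognostic role reasonable to expect. It does not show how strong the role is.

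**Working it through.** **Inputs from the article.** 316 enrolled, 90% with the outcome, 16 regions, ICC 0.025, d = 0.40 (SD taken as 1), two-sided α = 0.05.

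**Assumptions for this check.** 8 regions per arm, equal region sizes, two binary stratification factors with main effects of equal size, no separate provider variance, and no credit for baseline PF-CAT. R² is the share of between-region variance that the factors explain. It is not in the article, so it is varied from 0 to 1.

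**Step 1: the plan's own figure.**
- Evaluable patients: 316 × 0.90 = 284.4. Per region: m = 284.4 / 16 = 17.775.
- Design effect: 1 + (17.775 − 1) × 0.025 = 1.419.
- Effective n per arm: 142.2 / 1.419 = 100.2.
- SE = √(2 / 100.2) = 0.1413, and 0.40 / 0.1413 = 2.83.
- Normal-approximation power: Φ(2.83 − 1.96) = 80.8%, which reproduces the stated figure of about 80%. Solving for 80% power gives 307 enrolled, against 316.
- With a t reference on 14 region-level degrees of freedom, the same inputs give 75.0%. This fall comes from the reference distribution, not from the strata. It is the baseline for the comparison below.

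**Step 2: the most the strata can do.**
- Variance of a region mean: 0.025 + 0.975 / 17.775 = 0.025 + 0.0549 = 0.0799.
- Between-region share: 0.025 / 0.0799 = 31%.
- True SE of the stratified arm contrast: √{(2/8) × [0.025 × (1 − R²) + 0.0549]}. This is 0.1413 at R² = 0, 0.1298 at R² = 0.5 and 0.1171 at R² = 1.
- Even factors that explained all of the between-region variance would cut the SE by 17% (0.1171 / 0.1413 = 0.829).

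**Step 3: omit or include the strata.** Region means were simulated with 100,000 replicates per setting. Each of the four strata held four regions, two per arm. The analyses were a t test on 14 df without the strata and on 12 df with them.

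| R² | Power without strata | Power with strata | Type I error without strata |
|---|---|---|---|
| 0 | 74.8% | 73.8% | 4.9% |
| 0.10 | 75.1% | 75.2% | 4.7% |
| 0.25 | 75.3% | 77.2% | 4.1% |
| 0.50 | 75.8% | 80.8% | 3.2% |
| 0.75 | 76.3% | 84.3% | 2.4% |
| 1 | 76.9% | 87.9% | 1.8% |

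With the strata in the model, type I error is about 5% throughout. At R² = 0.50 the model without strata reports an average SE of about 0.140 against a true SE of about 0.130. Repeat runs moved these results by a few tenths of a point; type I error at R² = 0.50, for example, came out at 3.2% or 3.3%.

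**Step 4: the cost in degrees of freedom if the factors explain nothing.** Power is 75.0% on 14 df, 73.9% on 12 df (two binary factors) and 73.2% on 11 df (one further level).

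**The case against.** **The loss may be nil.** No section says how prognostic the factors are. The rank concerns low back pain only, while the trial also enrols neck pain, and nothing is offered for region size. Baseline PF-CAT, which is in the model, may absorb part of what the rank would explain. All of this stands. A reader might infer that precision is certainly lost, but below an R² of about 0.10 adjustment gains nothing and can cost about 1 point.

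**The direction is safe.** This stands too. A reader might infer a biased estimate or an invalid test. Neither follows, since omitting balanced factors makes the test conservative.

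**The size is easily overstated.** A larger assumed ICC gives larger gains, but it departs from the plan's 0.025. Nor is all conservatism of a fitted mixed model due to the omission. With the region variance bounded at zero, 18 patients per region and R² = 0.50, null rejection was 2.6% without the strata and still only 3.2% with them.

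**The sample size stands.** A reader might infer that 316 is wrong. The calculation never relied on adjusting for strata, and it reproduces.

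**The covariate rule is confined to sensitivity analyses.** A reader might infer that the primary model is chosen from observed imbalance. It is not, because its terms are fixed in advance. Whether the sensitivity covariates should be a fixed list is a matter of preference and is not pressed here.

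**A statistical analysis plan may add the strata.** It may, and it is not shown. But the article does not leave the model open: it lists the fixed covariate and the random effects. The point is about the model as stated.

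**Conclusion.** The mismatch is real: two factors constrain the randomisation of regions and neither is in the stated primary model. The consequence is conditional. If the factors are prognostic, the reported standard error is too large, the interval too wide and power lower than it need be.

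At the plan's ICC, adjustment gains about 2 power points if the factors explain a quarter of the between-region variance and about 5 points if they explain half. It costs about 1 point if they explain none. These figures rest on the assumptions listed with the check, above all two binary factors and no credit for baseline PF-CAT. The point is a worthwhile improvement to the model, not an error that undermines the trial.

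**What to change.** In the Statistical methods section, add region size and region low back pain outcome rank, coded as they were used in the randomisation, as region-level fixed effects in the primary PF-CAT model and in the secondary-outcome models. Name a small-sample degrees-of-freedom correction for the arm comparison. State the number of levels of each factor, since this sets the cost.

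The data are already held, because they were needed to randomise. With two binary factors, the region-level degrees of freedom fall from 14 to 12, a loss of about 1 power point if neither factor is prognostic. With more levels the loss is greater. No change to the sample size is needed on this ground.

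### The stated power of about 80% reproduces only when the 16-region limit on degrees of freedom is ignored; on 14 degrees of freedom the same inputs give about 75%, and the plan names no small-sample method for the arm effect

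*Protocol article*

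**What the plan says.** Under Design and setting, "Clinic regions are the unit of randomization", and the abstract gives their number: "A cluster randomized trial will randomly assign 16 clinic regions to either receive PNE training or continue with usual care".

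Under Statistical methods, the primary model adjusts for baseline PF-CAT, "with nested random effects for provider and clinic region to account for clustering by provider and the clinic regions". The level is fixed for all outcomes: "Statistical significance will be evaluating using a 2-sided α = 0.05 for both primary and secondary outcomes without adjustment for multiple comparisons". The section does not say whether the arm effect is referred to a normal or a t distribution, which degrees-of-freedom method applies, or whether REML or ML is used.

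Under Sample size and power calculations, the inputs are "we will power this study to detect an effect size of d = 0.40", "we assume an intra-cluster correlation of 0.025" and "We also assume that the primary outcome will be ascertained in 90% of enrolled patients". The result is that "316 enrolled patients will provide approximately 80% power" at a two-sided 0.05 level. No formula is named. The section adds that the gain from baseline adjustment is not credited, and concludes that the calculation probably errs a little on the safe side.

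**The concern.** Treatment is assigned to regions, so the arm effect is estimated from differences between regions. However many patients are enrolled, the variation between regions within arms is estimated from only 16 units. A power calculation that inflates the variance by a design effect but keeps the normal critical value allows for clustering in the variance and not in the degrees of freedom. With 16 clusters that difference is visible.

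Two things are at stake. The first is the power figure on which the enrolment target of 316 rests. The second is the primary test and, because the same 0.05 level applies, the secondary tests: a mixed-model test with a large-sample reference on this few clusters can reject too often and give intervals that are too narrow. The Discussion section acknowledges that randomising regions leaves fewer units, but draws only the consequence that more patients are needed.

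**Working it through.** **Inputs from the article.** Regions: 16. Enrolled: 316. Ascertained: 90%. Effect size: 0.40 (SD units). Intra-cluster correlation (ICC): 0.025. Two-sided level: 0.05. Baseline adjustment: not credited.

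**Assumed.** 8 regions per arm, equal region sizes, no separate provider variance.

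**1. Reproduce the stated power.**
- Analysed patients: 0.9 × 316 = 284.4.
- Patients per region: m = 284.4 / 16 = 17.775.
- Design effect: 1 + (m − 1) × ICC = 1 + 16.775 × 0.025 = 1.419.
- Effective number per arm: 284.4 / 1.419 / 2 = 100.2.
- Noncentrality: 0.40 × √(100.2 / 2) = 2.831.
- Power with a normal reference: Φ(2.831 − 1.960) = 80.8%.
- With the enrolled cluster size (316 / 16 = 19.75) in the design effect: 79.5%.
- With patient-level degrees of freedom (282): 80.5%.

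All three agree with the stated figure. Run in reverse, the normal formula asks for 307 enrolled, within 3% of 316.

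**2. Same inputs on region-level degrees of freedom.**
- Degrees of freedom: 16 − 2 = 14; critical value 2.145 instead of 1.960.
- Power from the noncentral t with noncentrality 2.831: 75.0%.
- Enrolment needed for 80% on 14 degrees of freedom: about 382.
- If region-level stratification terms enter the model, degrees of freedom fall further. At 12 the power is 73.9%; at 10 it is 72.3%.

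**3. What baseline adjustment would have to contribute.**
- 80% power on 14 degrees of freedom needs a noncentrality of 3.013.
- Variance reduction needed: 1 − (2.831 / 3.013)² = 11.7%.
- Baseline-outcome correlation: √0.117 = 0.34, if adjustment reduces region-level and patient-level variance in the same proportion.
- If it reduces only the patient-level part, the variance of the arm difference is (2/8) × [0.025 + 0.975 × (1 − r²) / m]. Power is then 79.9% at r = 0.41 and 80.2% at r = 0.42, so about 0.41 is needed.

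**4. Size of the test if a large-sample reference were used.** Simulation under no effect: 16 regions, 18 patients each, region random intercept, REML with the region variance truncated at zero, 400,000 trials per setting.

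| ICC | Level against z | Level against t, 14 df | Critical value giving 5% | Ratio to 1.960 |
|---|---|---|---|---|
| 0 | 4.0% | 2.5% | 1.87 | 0.95 |
| 0.01 | 5.0% | 3.3% | 1.96 | 1.00 |
| 0.025 | 5.9% | 4.0% | 2.04 | 1.04 |
| 0.05 | 6.6% | 4.6% | 2.11 | 1.07 |
| 0.10 | 6.9% | 4.9% | 2.13 | 1.09 |

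Patient-level degrees of freedom behave almost like z (5.8% at ICC 0.025). The upper limit is the exact t on 14 degrees of freedom: 7.0% beyond 1.96 and a ratio of 2.145 / 1.960 = 1.094. At low ICC the inflation is smaller because the region variance is often estimated as zero (about 21% of trials at 0.025), and the test then pools with the patient-level variance.

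**The case against.** A reader might infer from the power calculation that the primary test itself is planned as a large-sample test and will run at 6–7%. The documents do not support that. The Statistical methods section specifies a random-effects structure that includes the randomised unit and leaves the reference distribution open. A normal approximation at the sample-size step does not bind the later analysis; this calculation already differs from the planned model in omitting baseline and provider. The degrees-of-freedom method is also a detail that an article commonly leaves to the analysis plan, which is not shown, so its absence alone is not an error.

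A reader might also take the interval to be 9% too narrow. That is the limit at higher ICC; at the assumed 0.025 it is about 4%. At an ICC of 0.01 or below a z test is not liberal at all. The simulation is also simpler than the planned nested model, since it has no provider level and no baseline covariate.

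Finally, the article discloses that baseline adjustment is not credited, and a correlation of 0.34 to 0.41 would recover the lost power. That is fair, and it means the trial is not shown to be underpowered. But the article gives no such correlation, and baseline adjustment does nothing for the choice of reference distribution.

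What survives is the stated power figure, which does not depend on any unseen document.

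**Conclusion.** The point holds in a limited form. The stated power of about 80% ignores the 16-region limit on degrees of freedom. On 14 degrees of freedom the article's own inputs give about 75%, a loss of about 6 percentage points. The article weighs only the uncredited baseline gain when it calls the calculation somewhat conservative; the degrees of freedom push the other way, and nothing in the text shows which is larger.

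The effect on type I error is conditional. If the arm effect were tested against a normal or patient-level reference, the 5% level would be about 6% at the assumed ICC of 0.025 and about 6.6% at 0.05, with no inflation at 0.01 or below. The correct interval would be about 4% wider at 0.025 and up to 9% wider at higher values. With region-level degrees of freedom the test is not inflated and is slightly conservative at small ICC.

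These figures assume an 8:8 split, equal region sizes and no separate provider variance.

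**What to change.** In Sample size and power calculations, restate the power on region-level degrees of freedom (about 75% unadjusted with 316 enrolled). Alternatively, state the baseline-outcome correlation relied on to recover 80%: about 0.34 if the gain applies equally at region and patient level, about 0.41 if it applies at patient level only. Drop or justify the remark about conservatism accordingly.

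In Statistical methods, state that the arm effect in the primary and secondary mixed models is estimated by REML and tested with Kenward-Roger or Satterthwaite degrees of freedom reflecting the 16 regions. If the analysis plan already says so, a cross-reference is enough.

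Capping the degrees of freedom at the region-level value and adding a t test on baseline-adjusted region means are optional checks.

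The cost is a few sentences and a software option, with no new patients or data. The price is a slightly wider interval and a less favourable stated power.

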### Sample size and power calculations

We determined our sample size in order to detect a clinically relevant important effect on the PROMIS PF-CAT after 12 weeks with 80% power while accounting for clustering due to clinic regions. The literature on minimum clinically important differences for PROMIS scores is limited for spinal pain patient populations. In one study of 170 patients with LBP receiving spinal injections, Schalet [46] reported a difference in the mean T-score change of 4.5 vs. 1.7 on the PROMIS PF-CAT for patients reporting they were “better” vs. “worse” with a pooled change score SD of 6.4 (standardized effect size d = 0.43) [46]. Due to the lack of published data on meaningful effect sizes. we examined data from our own healthcare system and found a difference in T-scores for PROMIS PF-CAT of 4.2 vs. 0.72 for patients who reported improved vs. stable back pain based on concurrent Oswestry scores with a pooled SD = 6.9 (standardized effect size d = 0.50). Based on these studies, we will power this study to detect an effect size of d = 0.40. Based on reviews of past cluster randomized trials conducted in primary care settings, we assume an intra-cluster correlation of 0.025 [47, 48] to account for clustering of our primary outcome between the 16 clinic regions. We also assume that the primary outcome will be ascertained in 90% of enrolled patients. Under these assumptions, our cluster randomized design with 316 enrolled patients will provide approximately 80% power with 2-sided α = 0.05 to detect a mean difference in the PROMIS PF-CAT between clinic regions assigned to the PNE and usual care interventions. This calculation does not account for the savings in power that will result from adjusting for the baseline level of the outcome, and is therefore likely to be slightly conservative.

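### The stated 80% power is a large-sample figure; with 16 regions the same inputs give about 75% before baseline adjustment, and net conservatism is not shown

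*Protocol article*

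**What the plan says.** The section on sample size and power sets the target: "we will power this study to detect an effect size of d = 0.40". It assumes an intra-cluster correlation of 0.025 across the 16 clinic regions and primary outcome data on 90% of enrolled patients. It concludes that "our cluster randomized design with 316 enrolled patients will provide approximately 80% power with 2-sided α = 0.05". It gives neither the reference distribution nor the degrees of freedom. It adds that the gain from adjusting for the baseline score was not counted, so the calculation is "and is therefore likely to be slightly conservative".

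Two anchors support the effect size. The cited study has a "pooled change score SD of 6.4" and d = 0.43. The sponsor's own data have an SD of 6.9, described only as pooled, and d = 0.50.

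The design section makes the clinic region the unit of randomisation and stratifies by region size and by a regional outcome rank. The statistical methods section specifies a linear mixed model with baseline PF-CAT as covariate and "nested random effects for provider and clinic region to account for clustering by provider and the clinic regions".

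**The concern.** The treatment effect is a comparison between regions. However many patients each region contributes, 16 regions and two arm means leave 14 degrees of freedom for it. The two-sided 5% critical value is then 2.145 rather than 1.96, and a calculation that inflates the variance by a design effect but keeps 1.96 overstates power.

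The sentence on conservatism counts only the omitted factor that raises power, which is baseline adjustment. Three omitted factors lower it: the small number of regions, unequal region sizes (size is a stratification factor, so it varies), and clustering by provider, which is in the primary model but not in the power calculation. A reader is told which way the error runs without being given the means to check.

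At stake is an accurate statement of what the trial can detect. The validity of the planned comparison is not in question.

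**Working it through.** **Inputs from the article:** 316 enrolled, 90% ascertained, 16 regions, ICC 0.025, d = 0.40, two-sided α = 0.05.

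**Assumed here:** 8 regions per arm (the allocation ratio is not stated) and equal region sizes.

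**Step 1. Reproduce the stated figure.**
- Analysed patients: N = 316 × 0.90 = 284.4
- Per region: m = 284.4 / 16 = 17.775
- Design effect: DE = 1 + (m − 1) × ICC = 1 + 16.775 × 0.025 = 1.419
- Effective N: 284.4 / 1.419 = 200.4
- Noncentrality: d × √(effective N / 4) = 0.40 × √50.1 = 2.831
- Normal reference: Φ(2.831 − 1.960) = 80.8%

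This matches the stated figure. A t reference on patient-level degrees of freedom gives almost the same, 80.6%.

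**Step 2. Same noncentrality, between-region reference.**
- A noncentral t on 16 − 2 = 14 df gives 75.0%.
- If the two stratification factors entered the model, 13 df would give 74.5% and 12 df 73.9%.
- 80% power on 14 df needs a noncentrality of about 3.013, so the detectable d is 0.40 × 3.013 / 2.831 = 0.426.
- With d held at 0.40 and 16 regions, 80% would need about 343 analysed patients, or 343 / 0.90 ≈ 382 enrolled, without baseline adjustment.

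**Step 3. Add the planned baseline adjustment (14 df, equal sizes).** No correlation r between baseline and 12 weeks is given, so a range is shown. The gain depends on the SD scale of d.
- d in follow-up SD units: the variance factor is 1 − r².
- d in change-score SD units: differencing has already taken part of the gain, and the remaining factor is (1 + r)/2.

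The table applies the factor either to the whole variance or to the patient-level part only. In the second case DE becomes ICC × m + (1 − ICC) × factor.

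| r | Follow-up SD, whole | Follow-up SD, patient only | Change SD, whole | Change SD, patient only |
|---|---|---|---|---|
| 0.3 | 78.8% | 77.6% | 90.4% | 85.5% |
| 0.4 | 81.9% | 79.7% | 88.2% | 84.0% |
| 0.5 | 86.0% | 82.4% | 86.0% | 82.4% |
| 0.6 | 90.8% | 85.8% | 83.7% | 80.9% |
| 0.7 | 95.7% | 89.8% | 81.5% | 79.4% |
| 0.8 | 99.2% | 94.0% | 79.2% | 77.9% |

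On the follow-up scale, 80% is reached by r of about 0.35 (whole variance) or 0.42 (patient level only). On the change-score scale, power is at least 80% up to r of about 0.77 (whole variance) or about 0.66 (patient level only).

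**Step 4. Unequal region sizes (CV assumed; none is given).** DE = 1 + ((1 + CV²) × m − 1) × ICC. Power on 14 df without baseline adjustment:
- CV 0.3: DE 1.459, power 73.8%
- CV 0.5: DE 1.530, power 71.8%
- CV 0.7: DE 1.637, power 68.9%

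Provider clustering would lower power further. The article gives neither a provider-level correlation nor a number of patients per provider, so no figure is put on it.

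**The case against.** The strongest reply is that 75% belongs to an analysis that the trial will not run. The primary model includes baseline PF-CAT, the article discloses that its gain was left out, and most of the Step 3 table lies at or above 80%. The conservatism sentence therefore has a directionally valid reason and is hedged. The target d also lies below both anchors: at d = 0.43, unadjusted power on 14 df is about 81%. All of this stands. It limits the point to the unadjusted figure and to a claim of direction that has not been shown.

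Three stronger readings are tempting, and the documents do not support them.
- **The trial is underpowered.** A reader might infer this from 75%. It is not shown for the adjusted analysis, where a moderate baseline correlation makes up the loss.
- **The baseline gain is already spent because d is on a change-score scale.** Only the 6.4 is labelled a change-score SD. The 6.9 is not, and the scale of d = 0.40 is not stated. Even on that reading some gain remains.
- **The primary test will have an inflated type I error.** That would follow only from a large-sample Wald test, which the article does not specify. The degrees-of-freedom method may be in an analysis plan that is not at hand.

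The size CV is also an assumption. Region size is defined by weekly new evaluations, so the spread of analysed patients per region is unknown.

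**Conclusion.** The power statement is wrong as written for the inputs it lists. It holds only with a large-sample reference. On 14 df the unadjusted power is 75.0%, about five points below the stated level, and the detectable d is about 0.43 rather than 0.40. This rests on equal allocation of regions and equal region sizes; unequal sizes would lower it.

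The conservatism claim is undemonstrated, not false. Whether the planned analysis has more or less than 80% power depends on a baseline correlation and an SD scale that the article does not state, and on size variation and provider clustering that it does not count. Severity is minor to moderate, because neither enrolment nor the planned model changes.

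**What to change.** Restate the power as about 75% for d = 0.40 on 14 df before baseline adjustment, or state a detectable d of about 0.43 at 80% power. Replace the sentence on conservatism with net power at a stated baseline-to-12-week correlation, and say whether d is in follow-up or change-score SD units. Note that unequal region sizes and provider clustering lower the figure, for example to about 72% unadjusted at an assumed size CV of 0.5.

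As advice only: test the primary contrast with between-region or Kenward-Roger degrees of freedom, so that the analysis and the power statement use the same reference.

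The cost is a slightly less favourable published figure and a few sentences. No change to enrolment is needed.
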